## Abstract

**Background:**

Gestational Diabetes Mellitus (GDM) has well recognised adverse health implications for the mother and her newborn that are both short and long term. Obesity is a significant risk factor for developing GDM and the prevalence of obesity is increasing globally. It is a matter of public health importance that clinicians have evidence based strategies to inform practice and currently there is insufficient evidence regarding the impact of dietary and lifestyle interventions on improving maternal and newborn outcomes. The primary aim of this study is to measure the impact of a telephone based intervention that promotes positive lifestyle modifications on the incidence of GDM. Secondary aims include: the impact on gestational weight gain; large for gestational age babies; differences in blood glucose levels taken at the Oral Glucose Tolerance Test (OGTT) and selected factors relating to self-efficacy and psychological wellbeing.

**Method/design:**

A randomised controlled trial (RCT) will be conducted involving pregnant women who are overweight (BMI >25 to 29.9 k/gm^2^) or obese (BMI >30 kgm/^2^), less than 14 weeks gestation and recruited from the Barwon South West region of Victoria, Australia. From recruitment until birth, women in the intervention group will receive a program informed by the Theory of Self-efficacy and employing Motivational Interviewing. Brief ( less than 5 minute) phone contact will alternate with a text message/email and will involve goal setting, behaviour change reinforcement with weekly weighing and charting, and the provision of health information. Those in the control group will receive usual care. Data for primary and secondary outcomes will be collected from medical record review and a questionnaire at 36 weeks gestation.

**Discussion:**

Evidence based strategies that reduce the incidence of GDM are a priority for contemporary maternity care. Changing health behaviours is a complex undertaking and trialling a composite intervention that can be adopted in various primary health settings is required so women can be accessed as early in pregnancy as possible. Using a sound theoretical base to inform such an intervention will add depth to our understanding of this approach and to the interpretation of results, contributing to the evidence base for practice and policy.

**Trial registration:**

This trial is registered with the Australian New Zealand Clinical Trials Registry (ANZCTR): ACTRN12613000125729

## Background

The prevalence of Gestational Diabetes Mellitus (GDM) in Australia has been reported ranging from 1.7 to 9.6% [1-4] and it has been associated with significant rates of maternal and perinatal complications. Being overweight (a body mass index (BMI) of >25 kg/m^2^) or obese (BMI of >30 kg/m^2^) are recognised risk factors for developing GDM in pregnancy [5-8] and confer a 1.3 to 4.8 increased likelihood of developing this condition [6,8]. Maternal complications of GDM include an increased risk of developing Type 2 diabetes, metabolic syndrome and cardiovascular disease [5,9,10]. Newborns of pregnancies affected by GDM are at risk of macrosomia, shoulder dystocia, birth injuries and hypoglycaemia [11-13]; as young children they are at risk of becoming overweight, and in adolescence of impaired glucose tolerance and obesity [14].

In addition to developing GDM, women who are obese are at increased risk of many pregnancy related conditions including miscarriage, pre-eclampsia, hypertension, infection and thromboembolic disease [11,15-17] and have a greater chance of caesarean section [11,15,16,18-21], induction of labour [15,16,18,21] and death related to childbearing [11,19,21-23].

Compared to babies of women in a normal weight range, babies of overweight and obese women are more likely to be macrosomic [12,15,16,22,24], preterm [11-13,16,25], have a congenital anomaly [11-13,24], be admitted to the neonatal intensive care unit [11-13,25] and need treatment for jaundice or hypoglycaemia [11,16,17]. Thus, GDM particularly for those overweight and obese, increases both short and long term risks to the health of both the woman and her baby.

Over a third of pregnant women in Australia are either overweight or obese [2,6,11] and prevalence is higher in rural and regional areas than in metropolitan areas [6,26]; a prevalence of overweight and obesity of 65.5% has recently been reported in the pregnant population of north-east Victoria [6]. The rates of obesity are also increasing internationally [27] and identification of evidence based strategies to reduce the incidence of GDM and promote more healthy lifestyle choices in women who are overweight and obese needs to be prioritised to inform practice and health policy.

Healthy weight management for overweight and obese women includes avoiding excessive weight gain [28] and ideally aligning gestational weight gain to recommended ranges based on BMI [29-31]. However, intervention studies [32-35] have reported only a third to a half of obese women achieve a gestational weight gain within the recommended range [36,37]. Furthermore, there is limited evidence to support the effectiveness of dietary and physical activity lifestyle interventions in preventing adverse perinatal outcomes for obese women. In a systematic review of nine trials involving 743 women, Dodd and colleagues [38] concluded that the effectiveness of lifestyle interventions in pregnancy remains unclear. This is of significant concern and forms the rationale for trialling a different approach to preventing excessive weight gain in obese women.

There is a paucity of robust evidence to guide practice, with a limited number of published randomised controlled trials that have tested interventions with prevention of GDM as the primary outcome [39-41]. One of these trials [40], tested the effectiveness of a composite intervention versus usual care in preventing GDM. The intervention incorporated elements of continuity of care, measuring weight gain at each clinic visit, a regular five minute visit with a food technologist and a session with a clinical psychologist. The researchers concluded that the repetition of the intervention contributed to the positive outcomes. However, the intensive nature of the intervention, with a reliance on specialised staff, raises concerns regarding accessibility and sustainability in low socioeconomic status (SES) settings particularly rural and regional health care services.

Based on the approach of Social Cognitive Theory [42] and using the principles of Motivational Interviewing [43] we have developed a composite intervention that employs continuity of contact through weekly communication with the participating pregnant woman. The EDGE intervention (Educate, Develop Goals, Engage) modifies elements of Quinlivan et al. [40], specifically continuity of contact and reinforcement of behaviour modifications, and applies these to a format that can be trialled in areas of low SES and more broadly. The EDGE program will commence at recruitment and continue until birth.

We propose to explore the effectiveness of the EDGE intervention compared to usual care, in preventing the incidence of GDM in overweight and obese women. The results of this trial will contribute to our understanding of how to effectively facilitate healthy gestational weight gain in pregnancy, particularly in areas where there are issues of access to health care resources.

## Methods

This study will be conducted in the primary care setting of Barwon South West, Victoria, Australia. A RCT design will be employed where pregnant women will be individually randomised and allocated to either the intervention or a control group. The study will be conducted and reported using the CONSORT recommendations [44] (Additional file 1).

### Aims

The primary aim of this trial is to measure the impact of the EDGE intervention compared to usual care on the incidence of GDM in overweight and obese women. The primary hypothesis is that women randomised to the EDGE intervention will have 10% fewer diagnoses of GDM than women in the control group. There are four secondary aims: to measure the impact of the EDGE intervention compared to usual care on 1) restricting gestational weight gain to the weight ranges recommended by the Institute of Medicine [29]; 2) reducing the incidence of babies born large for gestational age (LGA); 3) differences in blood glucose levels taken at the Oral Glucose Tolerance Test (OGTT) and 4) promoting self-efficacy and selected factors for psychological well-being.

### Participants

Inclusion criteria: women with a singleton pregnancy will be included if their gestation is less than 14 weeks and their BMI ≥25. Exclusion criteria will include women: with pre-existing diabetes (types 1 and 2), a past history of gestational diabetes, unable to give informed consent in English, currently experiencing vaginal bleeding or with severe medical conditions preventing them from being able to undertake regular low impact exercise.

### Recruitment strategies

Women will be recruited from 30 participating general practices within the rural and regional area surrounding Geelong, Victoria. All women who meet the selection criteria will be informed of the study by the general practitioner (GP) or Practice Nurse (PN). Women interested in participating will be provided with a Participant Information and Consent Form and the GP/PN will obtain written informed consent and complete an enrolment form; both documents will be forwarded to the research office. All women enrolled in the trial will be given a study pack by the recruiting GP/PN that contains the first questionnaire with a reply paid envelope and a copy of the consent form.

### Randomisation procedure

A computer generated randomisation sequence will be used to facilitate the block randomisation of participants. Upon receipt of the consent and enrolment form by the research office, random allocation to the intervention or control group will be conducted by an individual who is independent to the study by drawing opaque numbered envelopes consecutively, to reveal the group allocation.

All women will receive written health information: 1) following recruitment and a reminder/thank-you for returning the questionnaire (Additional file 2) and 2) with a reminder/thank-you for returning the second questionnaire (Additional file 3). Both resources are used in clinical practice and are readily available.

Women allocated to the intervention group will receive the EDGE program from recruitment until birth, consisting of weekly contact with a brief (five minute) phone call each fortnight that employs Motivational Interviewing techniques on topics such as: identifying barriers and facilitators to positive behaviour change; encouraging goal setting; reinforcing positive lifestyle change; promoting self-monitoring and charting of weight gain and reflecting on behaviour change. The phone will alternate each week with text message/email contact to engage, support and reinforce behaviour change.

Women in the control group will receive usual care. Usual care in this setting involves initial weighing to calculate BMI [30]. There will be no change to clinical care beyond the ascertainment of weight from 36 weeks.

A reminder regarding weighing will be sent to all women with the second questionnaire.

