### Psychological health

Validated scales, where available, will be used to measure self- reported psychological wellbeing and engagement in behaviour change: anxiety; depression; self- efficacy and readiness to change behaviour will be measured at enrolment and at 36 weeks gestation using questionnaires in hard copy.

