### Data collection

A record review from the local hospitals will be conducted after birth to provide data for GDM and gestational weight gain outcomes. Socio-demographic data, pregnancy and birth data will be collected from the medical records and used descriptively to interpret findings. Data will also be obtained from medical records of General Practices if required.

Self-reported baseline and outcome data will be collected using a paper based questionnaire. The initial questionnaire will be provided at recruitment and the second questionnaire will be posted at 36 weeks; reply-paid envelopes will be provided for both questionnaires.

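### Allocation does not wait for the first questionnaire, so the baseline self-report scores of secondary aim 4 can be recorded after women know their arm

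*Protocol article*

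**What the plan says.** All references are to the Protocol article.

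- **Consent and enrolment (Recruitment strategies).** The general practitioner or practice nurse obtains consent and completes the enrolment form, and "both documents will be forwarded to the research office". The enrolled woman receives a study pack that "contains the first questionnaire with a reply paid envelope".
- **Trigger for allocation (Randomisation procedure).** "Upon receipt of the consent and enrolment form by the research office, random allocation to the intervention or control group will be conducted". The questionnaire is not part of this condition.
- **Follow-up of the first questionnaire (Randomisation procedure).** All women are sent written health information "following recruitment and a reminder/thank-you for returning the questionnaire".
- **Intended timing (Psychological health).** Anxiety, depression, self-efficacy and readiness to change "will be measured at enrolment and at 36 weeks gestation using questionnaires in hard copy".
- **Route (Data collection).** The first form is handed over when the woman is recruited and comes back by reply-paid post. It is supplied at recruitment; the text does not say that it is completed there.
- **Exposure and blinding.** EDGE runs from recruitment with weekly contact (Randomisation procedure), and women know their allocation (Blinding).

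**The concern.** A baseline measurement should be fixed before allocation can influence it. Here two sets of papers leave the practice by different routes. The consent and enrolment form goes to the research office and triggers allocation. The questionnaire goes home with the woman and comes back when she posts it. Nothing ties the second to the first.

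The scales are subjective, the respondents are unblinded, and EDGE aims directly at self-efficacy and readiness. A form filled in after the first calls may already carry some of the intervention's effect, or a reaction to being allocated to usual care. Using such a score as a baseline would subtract or adjust away part of what the trial wants to estimate. Without a completion date, the affected forms could not be identified later.

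**Working it through.** The plan gives no figure on this point. The sample size of 370 is set for GDM and does not bear on it. The check is therefore a comparison of the stated steps, followed by an illustration.

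**Step 1: the order of events as written**

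| Step | Condition stated | Waits for the questionnaire? |
|---|---|---|
| Consent and enrolment form forwarded | Completed by practice staff | No |
| Allocation | Receipt of that form | No |
| EDGE contact | Runs from recruitment | No |
| First questionnaire | Supplied at recruitment, returned by post | Not applicable |

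The Psychological health section gives enrolment as the time point, but no step secures it. A woman may complete the form at once, or after allocation and one or more EDGE contacts. Both are consistent with the plan.

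**Step 2: which analyses use the baseline scores**

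- Depression and Self-efficacy: mean differences between groups. Analyses: a t-test for continuous outcomes. Read as a comparison of 36-week means, this does not use the baseline.
- Analyses: regression with covariates that are not named. Baseline scores could enter here.
- Readiness to change: descriptive use only, so no adjusted effect estimate is planned.
- Baseline comparison (Analyses): the variables named are age, parity and BMI category. None comes from these scales.
- GDM, weight gain, large-for-gestational-age birth and plasma glucose: clinical or record-based, so untouched.

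**Step 3: illustration of size (all inputs assumed)**

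Let D be the true effect at 36 weeks, f the fraction of intervention women who complete the baseline after EDGE has begun, g the share of D they already show, and b the regression slope on baseline.

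- Spurious baseline gap = f × g × D
- Change-score estimate = D × (1 − f × g)
- Baseline-adjusted estimate ≈ D × (1 − b × f × g)

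| f | g | Loss, change score (f × g) | Loss, adjusted (b = 0.5) |
|---|---|---|---|
| 0.25 | 0.10 | 2.5% | 0.5 × 2.5% = 1.25% |
| 0.50 | 0.25 | 12.5% | 0.5 × 12.5% = 6.25% |
| 0.75 | 0.50 | 37.5% | 0.5 × 37.5% = 18.75% |

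In SD units, suppose 30% of forms are late and the arms differ by 0.3 SD among those forms. The baseline gap is 0.30 × 0.3 = 0.09 SD. A change score loses 0.09 SD; adjustment with a slope of 0.6 loses 0.6 × 0.09 = 0.054 SD.

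In these scenarios the early shift has the same direction as the final effect, so the bias is towards no difference. A shift in the opposite direction would reverse the sign.

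**Step 4: length of the questionnaire**

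The listed scales have 6 (anxiety) + 21 (depression) + 20 (eating self-efficacy) + 9 (exercise self-efficacy) + 12 (readiness) = 68 items. This matters for the cost of the fix.

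**The case against.** **The stated comparison does not need the baseline.** On its natural reading, the plan compares group means at 36 weeks with a t-test. Late baseline forms cannot bias that. No change-score analysis is stated, and adjustment for baseline scores is possible but not specified. This stands, and it limits the point to analyses that do use those scores.

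**Late return is not shown.** The mailing is a combined reminder and thank-you sent to everyone, so it does not prove that many forms will be late. The woman has the questionnaire in hand at recruitment, while allocation waits for paperwork to reach the research office, so many forms may be completed in time. This also stands. The order is left open, and the document gives no return times.

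**Detail may sit in the full protocol.** An article condenses, and handling of dates could be described elsewhere. That would excuse silence. Here, however, the article does state the trigger for allocation and the questionnaire's route, and followed exactly they do not deliver a measurement at enrolment.

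**Stronger readings.** A reader might infer that the trial can no longer show its groups were comparable before randomisation, or that its main results are biased. The documents do not support either. The comparability variables the plan names cannot be moved by a late questionnaire; at most, rows for these scales would be affected if they were added. The primary outcome does not pass through the questionnaire. A reader might also infer that return of the form will differ by arm. That is possible with unblinded women, but the document has no return data from which to assert it.

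**Conclusion.** The point holds in a limited form. The written sequence allows the first anxiety, depression, self-efficacy and readiness scores to be completed by unblinded women after allocation and after EDGE contact has begun, although the plan intends them for enrolment.

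The consequence is confined to secondary aim 4, and within it to change scores, baseline-adjusted regression and any baseline-table rows for these scales. It does not reach GDM, weight gain, large-for-gestational-age birth, glucose values or an unadjusted comparison of 36-week means.

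The size cannot be computed from the document. The figures above rest entirely on assumed fractions, early shifts and slopes, and show only that the loss could run from negligible to material. The point still deserves action before recruitment, because analysis cannot restore the timing of a baseline measurement.

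**What to change.** 1. Ask each woman to complete the first questionnaire at the consent visit, seal it, and have the practice forward it with the consent and enrolment form, so that it exists before the allocation envelope is drawn.
2. Do not hold allocation indefinitely if the questionnaire is not returned. A strict condition could delay or lose women for the primary outcome.
3. Record the date of completion and the date of allocation for every woman.
4. Do not use a questionnaire dated after allocation as a baseline value or covariate. Treat that baseline as missing, keep the woman in the analysis, and add a sensitivity analysis.
5. State whether baseline scores will enter the regression for these scales.

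The cost is a longer recruiting visit, since 68 items take more than a few minutes across 30 practices, and some missing baseline scores. No new data source is needed. If completion at the visit proves impractical, items 3 and 4 alone would deal with most of the problem.

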### Blinding

All participating women will provide written consent prior to randomisation however women will not be blinded to allocation. Due to the type of intervention, blinding of the researchers to allocation is also not realistic. Analysis will be performed by a person independent to the research team to avoid assessment bias.

### Primary outcome and measures

#### Gestational diabetes

The primary outcome is the proportion of women diagnosed with GDM between 24 – 28 weeks and will be defined using both the Australasian Diabetes in Pregnancy Society (ADIPS) management guidelines and the International Association of Diabetes and Pregnancy Study Groups (IADPSG) criteria. The use of different measures reflects the current controversy that exists in practice [3] and both measures will be reported.

Both ADIPS and IADPSG use a 75 gram glucose load. Using ADIPS criteria, GDM is diagnosed with a fasting plasma glucose level ≥5.5 mmol/L or a 2 hour level ≥8.0 mmol/L [45]. The IADPSG criteria diagnose GDM if any of the following levels are reported: a fasting plasma glucose level ≥5.1 mmol/L; a 1 hour level ≥10 mmol/L or a 2 hour level ≥8.5 mmol/L [46].

### Secondary outcomes and measures

#### Gestational weight gain

Differences in the proportions of women with gestational weight gain within the IOM (Institute of Medicine) guidelines [29] will be compared. Weight gain will be calculated as the difference between the booking-in weight and the last recorded weight from 36 weeks gestation to birth, as recorded in the pregnancy care records. IOM guidelines recommend women with BMI ≥25 to 29.9 kg/m^2^(overweight) gain 7–11.5 kilograms and women with a BMI ≥30 kg/m^2^ (obese) gain 5–9 kilograms [29].

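### The start weight for gestational weight gain is not tied to a time before randomisation, so for some women it may be measured after EDGE has begun

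*Protocol article*

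**What the plan says.** Under Gestational weight gain, the protocol article states: "Weight gain will be calculated as the difference between the booking-in weight and the last recorded weight from 36 weeks gestation to birth", with both weights "as recorded in the pregnancy care records". The outcome compared is the proportion of women whose gain lies within the IOM range for their BMI category: 7–11.5 kg if overweight, 5–9 kg if obese.

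The other relevant statements are spread over several sections:

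- **Source of the weights** (Data collection): "A record review from the local hospitals will be conducted after birth to provide data for GDM and gestational weight gain outcomes". General practice is a further source: "Data will also be obtained from medical records of General Practices if required".
- **Entry** (Participants): "women with a singleton pregnancy will be included if their gestation is less than 14 weeks and their BMI ≥25".
- **Who enrols, and where** (Recruitment strategies): "the GP/PN will obtain written informed consent and complete an enrolment form; both documents will be forwarded to the research office". Allocation follows once the research office has the forms (Randomisation procedure).
- **Start of the intervention** (Background): "The EDGE program will commence at recruitment and continue until birth". Randomisation procedure agrees: "Women allocated to the intervention group will receive the EDGE program from recruitment until birth".
- **Weighing in usual care** (Randomisation procedure): a first weighing from which BMI is worked out.

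No section gives a place or gestational week for the booking-in weight, or its order relative to enrolment or allocation.

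**The concern.** A change from baseline compares randomised arms cleanly when the baseline is fixed before allocation. EDGE targets weight directly, through goal setting, self-monitoring and charting of weight gain. A start weight recorded after it begins may already reflect it, and subtracting that weight takes out whatever EDGE did in the interval.

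Two consequences follow for secondary aim 1. The contrast in total gain would be diluted. Women would also be placed wrongly against the fixed kilogram limits, because gain between enrolment and booking-in is not counted in either arm. The interval may also differ between women, since it would depend on local booking practice. The researchers are not blinded to allocation (Blinding), which is a further reason to settle the baseline before allocation.

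**Working it through.** **The plan's own figure.** The article states no figure for weight gain. Its only sample-size figure, 370 women, concerns GDM. With 17% against 7%, two-sided 0.05 and 80% power, the two-proportion formula gives 165 per arm uncorrected and 185 per arm with continuity correction, so 370 reproduces. It does not depend on weight gain.

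**What the text permits.** Entry is in general practice before 14 weeks and EDGE starts at recruitment. The weight data come first from hospital records. Nothing requires the booking-in weight to predate allocation. Both orders are compatible with the text: booking-in at or before entry, or booking-in after EDGE has begun.

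**Dilution of the effect on gain.** Assume the EDGE effect accrues evenly by week. Let e be the enrolment week, b the booking-in week and t the week of the last weight. If b is later than e, the share of the effect removed is (b − e)/(t − e); otherwise it is zero. All weeks are assumptions, since the article gives neither the typical enrolment week nor any booking-in week.

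| e | b | t = 36 | t = 40 |
|---|---|---|---|
| any | at or before e | 0% | 0% |
| 12 | 14 | 2/24 = 8% | 2/28 = 7% |
| 10 | 16 | 6/26 = 23% | 6/30 = 20% |
| 8 | 20 | 12/28 = 43% | 12/32 = 38% |

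**Effect on the outcome actually compared.** The endpoint is the proportion within a two-sided range, so the loss above does not carry over directly. To illustrate, assume gain is normal with mean 11 kg and SD 5 kg, and that 0, 1 or 2 kg of it goes uncounted. The proportion within range is Φ((upper − m)/5) − Φ((lower − m)/5), with m = 11, 10, 9.

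- Overweight, 7–11.5 kg: 0.540 − 0.212 = 32.8%; 0.618 − 0.274 = 34.4%; 0.691 − 0.345 = 34.7%.
- Obese, 5–9 kg: 0.345 − 0.115 = 23.0%; 0.421 − 0.159 = 26.2%; 0.500 − 0.212 = 28.8%.

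The net change hides larger movements in opposite directions. For overweight women with 1 kg uncounted, those who truly gained 11.5–12.5 kg are wrongly counted as within range: 0.618 − 0.540 = 7.8%. Those who truly gained 7–8 kg are wrongly counted as below it: 0.274 − 0.212 = 6.2%. About 14% are misclassified, for a net shift of 1.6 points.

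**Direction.** Under this model the proportion within range is highest when the mean sits at the middle of the range: (7 + 11.5)/2 = 9.25 kg for overweight women and (5 + 9)/2 = 7 kg for obese women. Uncounted early gain raises an arm's proportion when its mean lies well above that point and lowers it when the mean lies below. The net effect on the difference between arms depends on where each arm's mean lies, which the article does not tell us.

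**The case against.** The strongest reply is that the fault is not on the page. The weight gain definition names no hospital, and no section places booking-in after enrolment. The trial is set in primary care, entry requires a known BMI, and usual care there includes a first weighing. The booking-in weight may be that same weighing, which would make it the pre-randomisation weight wanted here. General practice records are an allowed source, and a weight found in a hospital record need not have been measured at the hospital. A condensed article may also leave the measurement window to a fuller protocol.

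Most of this stands. A reader might infer that the plan uses a hospital weight taken weeks into EDGE, so that part of the effect is certainly subtracted. The article does not support that: the place and timing are open, and on a two-sided range the bias is not a simple subtraction. The proportion of women above the upper limit is also a tempting gauge of harm, but the plan compares the proportion within range.

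Two things remain. The article does more than omit a detail: it chooses the anchor and names the main source, and the rule as stated admits a post-randomisation baseline. A clearly pre-randomisation weight should already be available from the eligibility check.

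It is also fair to say that an enrolment weight misses gain before enrolment. That gain precedes randomisation, so it is balanced between arms in expectation. It limits the reading against the IOM ranges, not the comparison between arms.

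**Conclusion.** The point holds as a cheap improvement to one secondary outcome. The stated rule does not exclude a start weight measured after EDGE has begun. Where that happens, the contrast in total gain is diluted and women are misclassified against the IOM ranges. The dilution ranges from nil to about 43% across the assumed weeks, on the further assumption of even accrual. It is nil if booking-in always precedes randomisation. On the assumed normal distribution, the proportion within range moves by at most about 2 points in overweight women and 6 points in obese women when up to 2 kg goes uncounted. The direction of any bias in the difference between arms is undetermined. The documents establish none of these sizes. Secondary aim 1 alone is affected; the GDM outcome and the 370 women are untouched.

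**What to change.** Under Gestational weight gain, define the start weight as the weight measured by the GP or practice nurse for BMI eligibility at enrolment, before randomisation, and recorded on the enrolment form. Use the same weight for the BMI category that selects the IOM range. Use the booking-in weight only where the enrolment weight is missing and the booking-in weight predates randomisation. If booking-in already means the entry weighing, one sentence saying so is enough.

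The cost is one field on an existing form and one sentence in the protocol. Using general practice scales may add a small measurement error at the start point. Because the weight is taken before allocation, that error should not differ between arms.
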